### **9.7. Analysis methods – exploratory outcomes and analyses**

Any data that does not form a pre-specified outcome will be presented using simple summary statistics by intervention group (i.e. numbers and percentages for binary data and means (or medians) and standard deviations (or inter-quartile ranges) for continuous normal (or non-normal) data.

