The most recent and largest study was performed in 100 Indian children recently diagnosed with frequently relapsing SSNS 'eligible for therapy with long-term alternate day prednisolone with or without levamisole' [Gulati *et al*, 2011]. Children were recruited in stable remission, having received alternate day prednisolone 1.5mg/kg for 4 weeks, and then tapered by 0.25mg/kg every 2 weeks, until a dose of 0.5-0.75mg/kg on alternate days was reached. If a dose of prednisolone greater than 1mg/kg on alternate days was required, then levamisole was added. Children were randomised (stratified according to whether they received levamisole ( $n=32$ ) or not ( $n=68$ )) to either daily prednisolone for 7 days or to remain on alternate day prednisolone in an unblinded manner at the time of development of URTI (defined as fever  $>38^{\circ}\text{C}$ , rhinorrhoea or cough for  $>1$  day and diarrhoea for  $>2$  days). Children were reviewed every 2 months for a total of 12 months. The primary endpoint was the incidence of infection-associated relapse, with secondary

endpoints of infection frequency and type and cumulative dose of prednisolone. Patients exited the study if there were 2 or more relapses in any 6 month period. Daily prednisolone therapy at the time of URTI resulted in a reduction in the incidence of infection-associated relapse (0.7 vs. 1.4; rate difference: 0.7, 95% confidence interval (CI): 0.3 to 1.1;  $p < 0.01$ ) and the overall relapse rate (0.9 vs. 1.8; rate difference: 0.9, 95% CI: 0.4 to 1.4;  $p < 0.0001$ ). Whilst not powered to do so, a sub-analysis showed that this difference was lost in those receiving levamisole. Nineteen children in the daily prednisolone group vs. 7 in the alternate day group remained relapse-free over the entire 12 month study period ( $p = 0.03$ ). There was no difference in cumulative prednisolone dose between the two arms. More infections occurred in the daily prednisolone group (226 vs. 161;  $p = 0.04$ ), though no difference was detected in height SDS, Cushingoid features, cataract or serious infection. A total of 6 children (2 in daily steroid group) exited the study because of treatment failure necessitating treatment with cyclophosphamide or calcineurin inhibitors.

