#### 4.24 Monitoring of prednisolone related adverse effects

We will carefully monitor study subjects for prednisolone related adverse effects (see Appendix 2). As this is a Clinical Trial of an Investigational Medicine Product, we in any case need to document all adverse health events, their treatments and outcomes. Additionally to ensure that all adverse effects are recorded we will measure the following:

- i. Height will be carefully monitored at each study visit (with the exception of telephone or home study visits) using a calibrated stadiometer with the subject in bare or stocking feet.
- ii. Weight will be assessed at each study visit using calibrated scales.
- iii. Body mass index standard deviation score will be calculated from i] and ii].
- iv. Cushingoid features and hypertrichosis will be assessed by the clinician on a Likert scale and appetite will be assessed by the parent on a Likert scale.
- v. The presence or absence of striae will be documented at each study visit.
- vi. Behaviour will be assessed using the Achenbach Child Behaviour Checklist.
- vii. Blood pressure will be assessed at each study visit to document the incidence of hypertension.
- viii. Dipstick analysis of the urine will be performed at each study visit to look for glycosuria (**>5mmol/l**); where this is significant and persistent, plasma glucose will be measured in keeping with routine clinical practice.
- ix. The development of significant bacterial, viral and fungal infections will be documented.
- x. Use of varicella prophylaxis (zoster immune globulin or antiviral therapy) will be recorded.
- xi. We will prospectively collect information regarding all episodes of consultation with General Practitioners or hospital medical teams, including data on treatments prescribed or purchased. This will be incorporated into the costs measured as part of the health economic analysis.

If any of the above prednisolone related adverse-effects meet the criteria of an SAE the event must be recorded on the SAE form and faxed to the BCTU on [name] within 24 hours of the research staff becoming aware of the event. Please try to ensure that the local Principal Investigator has assigned causality to the SAE before reporting.

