| Gastrointestinal disorders                      |                                                                                                    |
| Very common                                            | Increased appetite, indigestion                                                                    |
| Musculoskeletal and connective tissue disorders |                                                                                                    |
| Uncommon                                               | Fractures, muscle-wasting, osteoporosis                                                            |
| Endocrine and metabolic disorders               |                                                                                                    |
| Common                                                 | Diabetes mellitus, glucose intolerance, hyperglycemias, reduced growth velocity, Cushingoid facies |
| Uncommon                                               | Cushing's syndrome, pituitary-adrenal axis suppression, pancreatitis                               |
| Dermatologic conditions                         |                                                                                                    |

|                                   |                                            |
|-----------------------------------|--------------------------------------------|
| Common                            | Hirsutism, hypo pigmentation, striae, acne |
| Neuromuscular and skeletal |                                            |
| Common                            | Arthralgia                                 |

Prednisolone is also associated with the following SAEs – predominantly in adult patients:

- Musculoskeletal: insufficiency fractures, avascular osteonecrosis
- Cardiovascular: premature atherosclerosis, myocardial infarction
- Gastrointestinal: ulceration and bleeding
- Central nervous system: psychosis
- Endocrine: hyperosmolar non-ketotic state, Addisonian crisis
- Miscellaneous: Bacterial infections, fungal infections, viral infections, ocular herpes zoster.

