### **9.6. Analysis methods – secondary outcomes**

The number of participants experiencing any relapse (i.e. both URTI-related and non URTI-related relapses), the number of participants having an escalation of background immunosuppressant therapy and the number of participants having a reduction of background immunosuppressant therapy will be presented and analysed as per the primary outcome measure.

The rate of URTI-related relapses and rate of any relapse will be presented in the first instance as numbers of participants who have a relapse with the respective percentage, and in the second instance as a median and IQR. An adjusted incidence rate ratio with 95% confidence interval will be estimated using a Poisson regression model. An offset for the length of time the participant was in the trial will be included in the model. Statistical significance of the treatment group parameter will be determined from the p-value generated by the model.

The cumulative dose of prednisolone received over the 12 month period will be presented as means with standard deviations and ranges. Adjusted mean differences along with 95% confidence intervals will be estimated using a linear regression model. Statistical significance of the treatment group parameter will be determined from the p-value generated by the model.

Adverse effect data will be tabulated at each time point (3, 6, 9 and 12 months) with statistical significance determined by a chi-squared or Fisher's exact test (as appropriate). We will also assess whether or not each adverse event occurred over the whole trial period by assessing all the 3, 6, 9 and 12 month data collectively.

Quality of life measures are taken at multiple time points, as is the Achenbach Behaviour Checklist Scores. Means and standard deviations will be summarised at each time point. Data will be analysed using mixed effect repeated measures models with the minimisation variable and the baseline questionnaire score included in the model as covariates. Time will be included as a continuous variable in the model. In the initial model, a treatment by time cross-term will be included in the model. If this is not significant, it will be considered that the treatment effect

is constant over time, and models without the treatment by time cross-term will be fitted. Adjusted mean differences between groups will be presented alongside the respective 95% confidence interval.

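### The SAP names no height SDS or growth comparison, leaves the promised BMI SDS underived and does not define hypertension by age, so a plausible steroid effect on growth could not be seen

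*Combined protocol and SAP*

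**What the plan says.** **Protocol.** Section 4.24 sets out how prednisolone adverse effects are captured. On height: "Height will be carefully monitored at each study visit (with the exception of telephone or home study visits) using a calibrated stadiometer". On weight: "Weight will be assessed at each study visit using calibrated scales". On BMI: "Body mass index standard deviation score will be calculated from i] and ii", where items i and ii are height and weight. Blood pressure is taken at each visit so that the incidence of hypertension can be recorded; no threshold by age is given. Appendix 2 includes growth in its list of common endocrine and metabolic reactions: "Diabetes mellitus, glucose intolerance, hyperglycemias, reduced growth velocity, Cushingoid facies". It lists hypertension as uncommon. Eligibility (4.2) runs from over 1 to under 19 years.

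**SAP.** Height, weight, BMI and blood pressure are not mentioned.
- Section 9.4 derives cumulative prednisolone dose, escalation or reduction of background therapy, and PedsQL scores. It derives no SDS.
- Section 9.6 handles adverse effects as categories, with Fisher's test as the alternative: "Adverse effect data will be tabulated at each time point (3, 6, 9 and 12 months) with statistical significance determined by a chi-squared". Its repeated-measures models are for quality of life and the behaviour checklist.
- Section 9.7 is the default for the rest: "Any data that does not form a pre-specified outcome will be presented using simple summary statistics by intervention group". For continuous data this means means and SDs, or medians and interquartile ranges.
- Section 9.1 adjusts outcomes for the minimisation factor and, where available, the baseline value.

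**The concern.** One of the evidence gaps that the protocol sets out to fill is whether repeated short courses increase prednisolone-related harm. Growth is a harm specific to children, the protocol's own appendix expects it, and the data to examine it are collected at clinic visits. The largest earlier trial that the protocol cites reported growth on an age-standardised scale: "no difference was detected in height SDS, Cushingoid features, cataract or serious infection".

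A chi-squared or Fisher test cannot take a continuous height unless a category is defined, and none is. That leaves by-arm summaries in centimetres over an 18-year age span, where most of the spread is age. Minimisation uses background therapy only, so nothing in the design narrows that spread. A real slowing of growth could pass unnoticed, and so could a gain from fewer relapse courses.

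**Working it through.** **1. Sample size to use.** The plan gives no figure for growth, so I take its evaluable number. Protocol 4.28: 50% v 32.5%, two-sided α = 0.05, 80% power. With pooled p̄ = 0.4125,

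n per arm = [1.960·√(2 × 0.4125 × 0.5875) + 0.842·√(0.5 × 0.5 + 0.325 × 0.675)]² / 0.175² = 123.04, rounded up to 124, or 248 in total.

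The plan states 250, and 250/0.70 = 357.1, or 358 as an even number (plan: 360). Both agree, so I use 125 per arm. The SAP applies the same modified ITT set to safety outcomes (5.3).

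**2. Formula.** Detectable difference at 80% power = (1.960 + 0.842) × SD × √(2/125) = 0.354 × SD. The 95% CI half-width is 1.960 × SD × √(2/125) = 0.248 × SD. With baseline adjustment, SD is replaced by SD × √(1 − r²), where r is the baseline-to-12-month correlation. The documents give no SD or r; those below are assumptions, shown as ranges.

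**3. Raw height at 12 months, unadjusted.**

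| Assumed SD (cm) | CI half-width (cm) | Detectable (cm) | Power for a 2 cm effect |
|---|---|---|---|
| 15 | 3.7 | 5.3 | 18% |
| 20 | 5.0 | 7.1 | 12% |
| 25 | 6.2 | 8.9 | 9% |
| 30 | 7.4 | 10.6 | 8% |

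For a 1 cm effect, power is 5–8% at SDs of 15–25 cm. The 1–2 cm effect is illustrative; the documents give no expected size. SAP 9.7 does not plan this interval. It is what a reader could construct from the means and SDs shown. With all 180 per arm, the detectable difference is still 4.4–7.4 cm for SDs of 15–25 cm.

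**4. Height SDS, adjusted for baseline SDS.**

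| Assumed SD | r | Residual SD | Detectable (SDS) |
|---|---|---|---|
| 1.0 | 0.95 | 0.312 | 0.11 |
| 1.2 | 0.95 | 0.375 | 0.13 |
| 1.0 | 0.90 | 0.436 | 0.15 |
| 1.2 | 0.90 | 0.523 | 0.19 |

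If one SDS is 5–6 cm (assumed), this is about 0.6–1.1 cm. A different route, change in SDS with an assumed SD of 0.3–0.5, gives 0.11–0.18 SDS.

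**5. Where the gain comes from.** Height SDS without baseline adjustment (SD 1.0–1.2) detects 0.35–0.43 SDS, or about 1.8–2.6 cm on the same conversion. Raw height with baseline adjustment, at SD 15–30 cm and an assumed r of 0.99–0.995, has a residual SD of 1.5–4.2 cm and detects about 0.5–1.5 cm. Adjustment alone therefore recovers much of the precision. Standardising adds a scale that means the same at every age and matches the earlier trial.

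**The case against.** The strongest reply is that the SAP is to be read with the protocol, and that height, BMI SDS and hypertension may already belong to the secondary outcome on incidence of prednisolone adverse effects. If so, SAP 9.7 does not apply, SAP 9.1 brings in baseline and the minimisation factor, and protocol 4.29 gives continuous secondary data mean differences, confidence intervals and baseline-adjusted models. Adverse effects are also scored on a proforma that is not in these documents.

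Part of this stands. The documents can be read that way, and on that reading the loss of precision would be small. But neither document names height as an outcome, 4.29 leaves full detail to the SAP, the SAP's only adverse-effect method is categorical, and no reference standard appears anywhere. Two readings leading to very different analyses are themselves a reason to settle the matter.

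A reader might infer more than the documents support:
- *That growth would go unreported.* It would not: 9.7 presents such data by arm, and 9.6 and 9.8 report adverse effects and events.
- *That raw means are confounded by age.* Allocation is randomised 1:1. Chance age imbalance costs precision; it does not bias the comparison.
- *That BMI would be analysed raw.* The protocol promises an SDS. The gap is that the SAP gives it no reference, derivation or comparison.
- *That blood pressure needs z-score models.* The protocol collects it for a binary incidence of hypertension, which 9.6 can tabulate. What is missing is a definition suited to age.
- *That the gain is simply the ratio of steps 3 and 4.* Those steps set an unadjusted analysis against an adjusted one, so the ratio is not like for like.

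**Conclusion.** The gap is real but bounded. Height has no age-standardised measure and no planned treatment comparison, the BMI SDS in the protocol is not carried into the SAP, and hypertension has no age-referenced definition for analysis. On the default in SAP 9.7, only differences of about 5–11 cm in mean height could be detected, against about 0.11–0.19 SDS from a baseline-adjusted analysis of the same data. These figures rest on 125 per arm and on assumed SDs and correlations. The contrast between an unadjusted raw comparison and a baseline-adjusted one persists across the ranges shown.

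No primary or efficacy conclusion depends on this. What is at risk is the safety statement: by-arm means that look similar should not be taken as evidence of no growth effect. I rate it as a cheap improvement worth making.

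**What to change.** In SAP 9.4, derive height SDS and BMI SDS from recorded values against a named age- and sex-specific reference, and state an age-referenced standard by which a recorded blood pressure counts as hypertension for analysis. This is an analysis definition only and changes no clinical management.

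In SAP 9.6, report for height SDS and BMI SDS the adjusted mean difference at 12 months with its 95% CI, with baseline SDS and the minimisation factor as covariates, as 9.1 already provides for outcomes. Tabulate hypertension incidence by arm with the method already in 9.6. State that height comes only from visits where it was measured, since protocol 4.24 excepts telephone and home visits, and give the number of children contributing.

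Cost: a few lines of SAP text and one derivation, with no new visits or measurements. Age can be calculated from the month and year of birth on the CRF (protocol 9.2); sex must also be in the analysis file. The downside is a few more safety comparisons in a plan that makes no multiplicity correction (SAP 5.2), so these should be read as estimates with intervals.

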### **9.8. Safety data**

The number and percentage of participants experiencing any adverse events, serious adverse events (SAEs) and suspected unexpected serious adverse reactions (SUSARs) will be presented by intervention group. Statistical significance will be determined by a chi-squared or Fisher's exact test (as appropriate). A table listing the SAEs including information on the nature of the event and whether or not it was deemed related to the trial treatment will be provided.

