- ii] Whether this effect occurs in children receiving long term maintenance prednisolone therapy in conjunction with other immunosuppressive therapies e.g. levamisole, ciclosporin, tacrolimus and MMF;

- iii] Whether this effect occurs in children receiving levamisole, ciclosporin, tacrolimus, and MMF without long term maintenance prednisolone therapy;
- iv] Whether this effect occurs in children on no long-term immunosuppressive therapy;
- v] Whether there is an increase in the incidence of prednisolone-related adverse effects, including behavioural abnormality associated with the use of this intervention;
- vi] The cost-effectiveness analysis of such an approach, using a decision-analytic modelling approach.

A meeting was convened in January 2012 to discuss this study to which the members of the NIHR Medicines for Children Research Network (MCRN) Nephrology Clinical Studies Group, representing each of the 13 tertiary paediatric nephrology centres in the UK were invited to attend. A number of consumer representatives, including the Chairperson of the UK Nephrotic Syndrome Trust (NeST), and other parents of children with nephrotic syndrome were also in attendance. It was clear from this meeting that interest not only lay in the two cohorts originally included in the expression of interest, but also in those receiving other immunosuppressant therapies (with or without prednisolone) for their nephrotic syndrome. A single pragmatic trial was designed to include all patients with relapsing SSNS, in order to answer the overarching question of whether treatment with a short course of daily prednisolone at the time of upper respiratory tract infection (URTI) in children with relapsing SSNS reduces the subsequent development of nephrotic syndrome relapse. The results of the study will therefore be widely generalisable.

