### **3.2 Research question**

Does a six day course of daily prednisolone given early in the course of URTI in children with relapsing SSNS effectively and safely reduce the incidence of subsequent URTI-related relapse?

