#### **4.29 Statistical Analysis**

The Statistical Analysis Plan describes the planned analyses for PREDNOS 2 in full detail. A summary of the main analysis methods are described here.

The primary endpoint is the first URTI-related relapse of nephrotic syndrome (URT-related relapse is defined as 3 days of Albustix 3+ proteinuria within 14 days of onset of an URTI) which occurs during the 12 month follow-up period. The proportion of subjects that experience an URTI-related relapse will be calculated for the two study treatment arms, and compared using a chi-squared test. Treatment effects will be expressed as relative risks with 95% confidence intervals.

This was chosen as the primary endpoint as it is hypothesised that giving daily prednisolone at time of URTI will reduce the subsequent development of disease relapse. If this hypothesis is correct, then those subjects randomised to placebo will experience more URTI-related relapses than those subjects randomised to active drug. This would mean that subjects in the placebo arm are more likely to undergo intensification of immunosuppressive therapy. This in turn would reduce the chances of the subjects in the placebo arm from having further relapses (both URTI-related and non URTI-related) which introduces bias. Therefore, all subjects will be followed-up for 12 months to also assess the relapse rates between the two treatment arms over a 12 month period as a secondary endpoint, but due to these potential biases, the primary endpoint will focus on the first URTI-related relapse. The analysis of the secondary endpoints for relapses per year will assess incidence (relapse) density rates for the two treatment arms and rate differences will be calculated for both URTI and non-URT related relapse of nephrotic syndrome over the 12 month follow-up period. Appropriate regression analysis (e.g. Poisson) will be used to compare relapse rates in the two treatment groups, should there be an imbalance in any important co-variables (e.g. URTI rates across the two study arms).

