The secondary endpoints include both continuous and categorical data items. The dichotomous data (e.g. incidence of escalation of background immunosuppressive therapy) will be analysed as per the primary outcome. Continuous data (e.g. prednisolone dose, quality of life scores) will be expressed as means and standard deviations, with differences in means and 95% confidence intervals. Longitudinal plots of the data over time will be constructed for visual presentation of the data. Data will be analysed using mixed effect repeated measures models with the interventions specified as independent variables. Baseline data will be included in the model as a covariate.

Analyses will be of all randomised subjects using intention to treat, except for those who do not have an URTI following randomisation. Over the course of the study up to the 12th July 2016, the number of patients who have completed the trial without experiencing at least one URTI is approximately 24% which is higher than the originally estimated <10% at the start of the trial. Exclusion of these subjects will result in no bias as these drop-outs are not related to the treatment and should by chance be equally distributed across the two treatment arms (this will be monitored throughout the trial). Sensitivity analyses will be performed on the 12 month data analyses due to the issues raised above. These analyses will be fully outlined in the Statistical Analysis Plan, and will include analyses with subjects censored at point of treatment escalation.

The only subgroup analyses planned are by the background treatment regimen that the subjects are on at randomisation (no long-term treatment; on long term maintenance prednisolone therapy; on other immunosuppressant therapy with long term maintenance prednisolone therapy; on other immunosuppressant therapy without prednisolone); an analysis comparing those subjects on prednisolone versus those not on prednisolone; and an analysis comparing those subjects on other immunosuppressant therapy versus those not on other immunosuppressant therapy. The study is not powered to detect differences in treatment effect across these subgroups, so these analyses will be considered as hypothesis generating.

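### Binary safety outcomes get counts and an unadjusted p-value but no effect estimate or confidence interval, at odds with protocol 4.29 and SAP 9.1

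*Combined protocol and SAP*

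**What the plan says.** Safety is part of the question. Protocol 3.2 asks whether the six-day course can "effectively and safely reduce the incidence of subsequent URTI-related relapse". Protocol 3.1 lists this among the questions earlier trials left open: "Whether there is an increase in the incidence of prednisolone-related adverse effects, including behavioural abnormality associated with the use of this intervention". Incidence of SAEs and incidence of prednisolone adverse effects are secondary outcomes iv and v in SAP 4.4.

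For these outcomes the SAP plans the following.

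- **SAP 9.8:** counts and percentages of children with adverse events, SAEs and SUSARs are shown by group. The section then says "Statistical significance will be determined by a chi-squared or", with Fisher's test as the alternative. SAEs are also listed with their nature and relatedness.
- **SAP 9.6:** "Adverse effect data will be tabulated at each time point (3, 6, 9 and 12 months) with statistical significance determined by a chi-squared or", again with Fisher's test as the alternative. The section adds a yes/no assessment of each effect over the whole trial period and names no effect measure for it.

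Three other passages bear on the same outcomes.

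- **Protocol 4.29:** dichotomous secondary data "will be analysed as per the primary outcome", and for the primary outcome "Treatment effects will be expressed as relative risks with 95% confidence intervals".
- **SAP 9.1:** intervention effects for all outcomes are adjusted for the minimisation factor, background therapy.
- **SAP 5.1:** every between-group estimate carries a two-sided 95% interval.

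**The concern.** A chi-squared or Fisher p-value tests whether the arms differ. It does not say by how much, or how large an excess the data still allow. In a trial sized for its efficacy endpoint, a non-significant safety comparison can mean that there is no excess, or that an excess was there and the trial was too small to show it. The p-value does not distinguish the two, whereas an estimate with its interval shows the range of excess harm that remains compatible with the data.

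Protocol 3.1 says that a finding that the course works effectively and safely would alter practice in the UK and other developed nations. Protocol 7.1 and section 8 both acknowledge the risk of extra steroid exposure without benefit. Protocol 3.1 also calls adverse event reporting in the earlier trials sparse. The safety statement therefore deserves the same form of result as the efficacy statement.

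**Working it through.** **1. Which outcomes have an estimate.** SAP 9.5 and 9.6, read outcome by outcome:

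| Outcome | Planned between-arm result |
|---|---|
| URTI-related relapse (primary); any relapse; escalation; reduction | Adjusted risk difference and relative risk, 95% CI |
| Relapse rates | Adjusted rate ratio, 95% CI |
| Cumulative prednisolone dose | Adjusted mean difference, 95% CI |
| Achenbach behaviour; quality of life | Adjusted mean difference, 95% CI |
| AEs, SAEs, SUSARs; tabulated adverse effects | n (%) and chi-squared or Fisher p-value |

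Only the last row has no estimate, and its test is also unadjusted. SAP 5.1 does not fill the gap: it attaches an interval to an estimate, and none is named here. Protocol 4.29 also uses a chi-squared test, so the test itself does not breach the protocol. What is missing is the relative risk and its interval.

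**2. The plan's own sample size.** Inputs from SAP 4.7: 50% vs 32.5%, two-sided 5%, 80% power.

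n per arm = [1.96·√(2·p̄·q̄) + 0.842·√(p₁q₁ + p₂q₂)]² / (p₁ − p₂)², with p̄ = 0.4125

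= [1.96·√0.4847 + 0.842·√0.4694]² / 0.0306 ≈ 123.0, rounded up to 124, or 248 in total (stated: 250). Then 250/0.7 = 357.1, or 358 (stated: 360). The figures reproduce. No calculation is given for any safety outcome.

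**3. Power for a true doubling of a binary harm.** Evaluable children per arm: 125 (half of 250). If only the 24% without an URTI (protocol 4.29) are lost, 180 × 0.76 ≈ 137. With no exclusions, 180. The documents give no SAE or adverse-effect rate, so the control rates are assumptions. The normal approximation at 125 per arm for 5% vs 10% is

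Φ{[0.05 − 1.96·√(2·0.075·0.925/125)] / √[(0.0475 + 0.09)/125]} = Φ{(0.05 − 0.0653)/0.0332} = Φ(−0.46) ≈ 0.32.

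Exact enumeration of the binomial outcomes gives these powers (chi-squared / Fisher, %):

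| Control → active | 125 per arm | 137 per arm | 180 per arm |
|---|---|---|---|
| 2% → 4% | 13.1 / 6.6 | 14.1 / 7.6 | 18.7 / 11.3 |
| 5% → 10% | 31.9 / 23.5 | 35.1 / 26.5 | 44.1 / 36.1 |
| 8% → 16% | 49.7 / 42.2 | 53.7 / 46.8 | 65.7 / 58.9 |
| 10% → 20% | 60.2 / 53.8 | 64.9 / 58.9 | 76.8 / 71.7 |
| 15% → 30% | 81.7 / 77.7 | 85.4 / 81.7 | 93.3 / 91.5 |
| 20% → 40% | 93.7 / 91.9 | 95.5 / 94.2 | 98.8 / 98.3 |

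By the normal formula, power for a doubling passes 50% at a control rate of about 8.1% (125 per arm), 7.5% (137) or 5.8% (180). It reaches 80% at about 14.6%, 13.6% and 10.9%. With Fisher's test at 125 per arm, the 50% point lies between 8% and 10%.

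**4. What the interval adds.** Assume SAEs in 12/125 active and 6/125 placebo.

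- Planned test: z = 0.048/√(0.072·0.928·2/125) = 1.47, p = 0.14; Fisher p = 0.22.
- Relative risk 2.0. SE of its log = √(1/12 − 1/125 + 1/6 − 1/125) = 0.484. 95% CI 0.77 to 5.16.
- Risk difference 4.8 points. SE = √(0.096·0.904/125 + 0.048·0.952/125) = 0.0326. 95% CI −1.6 to 11.2 points (Wald).

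The result stays non-significant, but the interval shows that an excess of about 11 points, or a fivefold risk, is not ruled out. At twice these counts (24 vs 12), p = 0.031 and the relative risk is 2.0 (1.05 to 3.82).

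**The case against.** The other side has substantial points.

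- **Safety does not rest on p-values alone.** A reader might infer that it does. The documents say otherwise: Achenbach behaviour, part of outcome v, and cumulative prednisolone dose have adjusted mean differences with intervals, and counts by arm and an SAE listing are planned. This stands, and it confines the point to binary harms.
- **A doubling would not necessarily be missed.** A reader might infer that it usually would be. That depends on a rate the documents do not give. Protocol 5.3 generally treats an overnight hospital stay as serious, so a rate below 8% cannot be presumed. At a control rate of 15%, power exceeds 80% by the chi-squared test. This stands.
- **The low power comes from sample size, not from the missing interval.** The fix changes none of the powers above. An unadjusted relative risk can also be worked out from the counts the SAP already reports. This stands too. What is lost is the pre-specified, adjusted estimate and its place in the report.
- **The documents partly cover it.** SAP section 1 says to read the SAP with the protocol, and SAP 9.1 and 5.1 set general rules. But an analyst following the specific text of 9.6 and 9.8 would produce no estimate, so the sections have to be reconciled.
- **Objective iv is framed as a reduction in adverse effects, which a two-sided test fits.** It does, but the open question in protocol 3.1 is whether adverse effects increase, and by how much is what a reader needs.

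Nothing in the documents says that a non-significant result will be reported as proof of safety, and that should not be presumed.

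**Conclusion.** The point holds for binary harms. For SAEs and the tabulated prednisolone adverse effects, SAP 9.6 and 9.8 specify counts and an unadjusted p-value where protocol 4.29 calls for a relative risk with a 95% interval and SAP 9.1 for adjustment by background therapy. The SAP's change table gives no reason for treating harms differently from the other binary secondary outcomes.

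The practical weight depends on the event rate. At 125 per arm a true doubling is more likely than not to be non-significant by the chi-squared test only if the control rate is below about 8%. The limit is somewhat higher with Fisher's test and lower (about 6% to 7.5%) with 137 to 180 per arm. In that range a p-value alone may not exclude relevant harm. Above it the test is progressively more informative, and the case for the estimate rests on consistency and clear reporting. These figures assume equal arms, a two-sided 5% test and control rates that the documents do not supply.

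**What to change.** In SAP 9.6 and 9.8, for SAEs and for each prednisolone adverse effect (occurred or not over the 12 months), report the risk difference and relative risk, active vs placebo, with 95% confidence intervals. Use the binomial models of SAP 9.5 adjusted for background therapy. Where events are too sparse for these models, give unadjusted exact or score intervals and say so. Add one sentence stating that safety will be interpreted from the estimate and its interval, and that a non-significant test will not be taken as absence of harm.

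The chi-squared or Fisher p-values and the visit-by-visit tables can stay; whether to keep them is a matter of reporting style.

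The cost is SAP wording and a few more model runs on data already collected, with no new patients or procedures and no change to the primary analysis. The downside is that the safety statement may read less favourably, for example that a doubling cannot be excluded.
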